**Methods:**

This is an approved open-label, multicenter, randomized controlled trial to compare the effectiveness of intranasal versus intravenous dexamethasone administered in low doses to moderate and severe COVID-19 adult patients. The protocol is conducted in five health institutions in Mexico City. A total of 120 patients will be randomized into two groups (intravenous vs. intranasal) at a 1:1 ratio. Both groups will be treated with the corresponding dexamethasone scheme for 10 days. The primary outcome of the study will be clinical improvement, defined as a statistically significant reduction in the NEWS-2 score of patients with intranasal versus intravenous dexamethasone administration. The secondary outcome will be the reduction in mortality during hospitalization.

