#### Outcomes

The expected primary outcome is clinical improvement, defined as a two-point improvement in the ordinal scale regarding the initial NEWS-2 score. This is an adapted score recommended by the World Health Organization (WHO) and the National Institute for Health and Care Excellence (NICE) to facilitate the early recognition and escalation of deteriorating patients [55, 56]. Although this score is commonly adopted for triage, it can also be used for continuous assessment, particularly in predicting intrahospital mortality. In this context and based on previous experimental data regarding the sustained effect of intranasal dexamethasone, we decided to evaluate the improvement in the initial NEWS-2 score as the first outcome.

The secondary expected outcome includes a reduction in mortality that will be examined during treatment (after randomization), a reduction of the time required for mechanical ventilation, the length of patient’s stay in the hospital, 30-day post-discharge mortality, and intrahospital complications. Viral load, the immune-inflammatory profile, and other physiological parameters will also be evaluated before and after treatment (see above).

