#### Statistical analysis

Descriptive statistics using mean (standard deviation) or frequency (percentage) will be used following the dimension scale of the variable. An initial comparison between the hospital will define relevant differences among them. Since healthcare conditions are variable in each hospital included in this study, we will analyze the results with a multilevel mixed longitudinal model. The outcome analysis for NEWS-2 components (i.e., respiration rate, oxygen saturation, systolic blood pressure, pulse rate) will be done using the last observation carried forward (LOCF) in those subjects with at least two observations, this analysis will avoid over-optimistic estimates of efficacy. Other efficacy variables like biochemistry or cell counts will be analyzed without ITT due to the susceptibility to type II error.

Biochemical variables and cell counts will be aggregated using principal component analysis and use the scores if the Kaiser-Meyer-Olkin (KMO) is greater than 0.6 and sphericity *p* < 0.0001. The scores using varimax rotation will be used as dependent variables if the method is suitable for our data. The longitudinal mixed model can be described as:
$$ {y}_{ij}={X}_{ij}\beta +{u}_i+{v}_{j(i)}+{\epsilon}_{ij} $$

where *j* = 1,..,Ti are nested in 10 time points, within *i* = 1,..,5 hospitals. The Xs correspond to fixed variables like the treatments, age, sex, and weight, among other confounders.

A database in vertical format was reshaped to nest the biochemical, inflammatory markers, cell count adjusted by sex, age, and BMI. We will perform restricted maximum likelihood (REML) estimation in case we obtain balanced samples. However, if we obtain an unbalanced sample, we will use maximum likelihood instead [59]. Because we expect a small sample size from some hospitals, we will make inferences using the Kendward-Roger degrees of freedom method. We will make simultaneous inferences about l linear combinations of fixed factors. Despite the complicated situation where *l* > 1 we will consider:
$$ F=\frac{1}{l}{\left(\hat{\beta}-\beta \right)}^T\ L{\left({L}^T\ {\hat{\varphi}}_AL\right)}^{-1}\ {L}^T\ \left(\hat{\beta}-\beta \right) $$

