The internal random structure [$$ {L}^T\ {\hat{\varphi}}_AL $$] can change in different settings, but still will be a good approximation. Simulations studies showed adequate performance of modifications with different REML [60]. Finally, the structure of residual error will be analyzed within the lowest-level group. Once recognized, the covariance structure we will use unstructured, Toeplitz, or exponential corrections. This approach will give unbiased approximation even in presence of unbalanced samples.

The residuals for our mixed models will be considered by the source of present variability: The marginal residuals will predict the marginal errors, the conditional residuals, and the best linear unbiased predictor (BLUP) residuals. The conditional residuals will be standardized with:

$$ {\hat{\varepsilon}}_k^{\ast }=\frac{{\hat{\varepsilon}}_k}{\sigma\ \sqrt{p_{kk}}} $$ , where *p*_*kk*_ represents the *k*th element of the covariance structure. These residuals are functions of the joint leverage of fixed and random effects.

Subgroup analysis will be based on interaction as secondary analysis. This information will help to identify multiplicative effects from basal conditions like the presence of type 2 diabetes, obesity, hypertension, clinical history IECA medication, or other conditions.

All analysis will describe the number of patients with the outcome of interests, the treatment effect (mainly using eta squared), additive and multiplicative interactions with 95% confidence intervals, and the direction of the interaction (positive or negative) by specific subgroups. The analysis will be performed with Stata version 17.0 [StataCorp LLC College Station TX]. A statistical difference with *P* < 0.05 will be considered significant.

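### The covariates named for the mixed model do not include baseline NEWS-2, the score from which the primary outcome is measured

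*Protocol article*

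**What the plan says.** The Statistical analysis section of the protocol article states that "we will analyze the results with a multilevel mixed longitudinal model". It writes out the equation, with a hospital term, a term for observations nested in hospital and a residual. The index j is said to run over observations that "are nested in 10 time points, within" five hospitals; no patient index is written. The fixed part is described once: "The Xs correspond to fixed variables like the treatments, age, sex, and weight, among other confounders". The only interactions planned are those for subgroups: "Subgroup analysis will be based on interaction as secondary analysis".

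The Outcomes section has the primary outcome as clinical improvement, "defined as a two-point improvement in the ordinal scale regarding the initial NEWS-2 score". The abstract words it as a comparison of scores, "defined as a statistically significant reduction in the NEWS-2 score of patients with intranasal versus intravenous dexamethasone administration". Neither place gives a day of assessment. Treatment lasts 10 days in both arms ("Both groups will be treated with the corresponding dexamethasone scheme for 10 days"). The Eligibility criteria require NEWS-2 of at least 5, so the score exists for every patient at entry. The Procedures and Data collection sections have clinical data recorded daily.

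**The concern.** The article names age, sex and weight but not the score from which its own primary outcome is counted. Subtracting baseline to form the outcome is not the same as adjusting for it. Patients enter because their score is high, so later improvement depends on the starting value, through regression to the mean and through how far the score can fall. With 60 patients per arm, a chance difference in starting scores adds noise to the treatment comparison, and a baseline covariate would remove much of it at no cost.

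A second, conditional matter concerns time. A treatment term without treatment-by-day gives one coefficient averaged over the modelled days. Since no passage says on which day the arms are to be compared, the reader cannot tell whether that average is the intended quantity.

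**Working it through.** **The plan's own figure.** The only design figure is 60 per group, from 70% versus 45% free of mechanical ventilation. The two-sided 5%, 80% power, uncorrected formula, with mean proportion 0.575, gives

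[1.96·√(2·0.575·0.425) + 0.8416·√(0.70·0.30 + 0.45·0.55)]² / 0.25² = (1.370 + 0.569)² / 0.0625 ≈ 60.2, so 61 per arm before losses.

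That is close to the stated 60. It does not rest on NEWS-2, so it cannot measure the loss discussed here.

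**Inputs.** From the article: 60 per arm, 1:1 allocation, P < 0.05, 80% power, 10 time points, 10 days of treatment. Assumed, because the article gives none of them: the correlation r between baseline and follow-up NEWS-2 (0.3 to 0.7), equal SDs at both times, and the time course of the effect.

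**Baseline, continuous score, one follow-up day.** In units of the single-day variance:

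- raw follow-up score: 1
- change from baseline: 2(1 − r)
- baseline-adjusted (ANCOVA): 1 − r²

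The adjusted-to-change variance ratio is (1 − r²)/[2(1 − r)] = (1 + r)/2. The SE penalties are therefore √[2/(1 + r)] for change and 1/√(1 − r²) for the raw score.

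| r | adjusted/change variance | SE penalty, change | SE penalty, raw | power after adjustment if the raw analysis has 80% |
|---|---|---|---|---|
| 0.3 | 0.65 | 24% | 5% | 84% |
| 0.5 | 0.75 | 15% | 15% | 90% |
| 0.7 | 0.85 | 8% | 40% | 98% |

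The last column is Φ(2.80/√(1 − r²) − 1.96).

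Detectable difference at r = 0.5 with 60 per arm: unadjusted, 2.80·√(2/60) = 0.51 SD, the same for raw and change scores because 2(1 − 0.5) = 1. Adjusted: 0.511·√0.75 = 0.44 SD.

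**Time course.** A single treatment coefficient estimates the mean of the daily effects. Taking the day-10 effect as 1 and averaging days 1 to 10:

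- constant effect: 1.00
- linear rise to full by day 3, then constant: (1/3 + 2/3 + 8)/10 = 0.90
- onset at day 5, then constant: 6/10 = 0.60
- linear growth from day 0: (0.1 + 0.2 + … + 1.0)/10 = 0.55

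A smaller average need not mean less power, because averaging also reduces the variance. Suppose the day-10 contrast has 80% power and the between-day correlation is 0.3 to 0.9. The averaged contrast then has 84% to above 99% power for a constant effect. For linear growth it has 72% down to 37% under compound symmetry, or 96% down to 44% under AR(1).

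**The case against.** The strongest reply is that the covariate list is illustrative. It is introduced as examples and closed with a reference to further confounders, and a condensed article may leave the full list to an analysis plan that is not shown. This stands in part: a reader might infer that the model omits baseline NEWS-2, day and treatment-by-day, but the text shows only that they are not named. The section also plans joint tests of several fixed-effect contrasts, which would fit a model with treatment-by-day terms without proving one. The article is not merely silent, however. It prints the equation, the degrees-of-freedom method, candidate covariance structures and some covariates, and the most relevant covariate is not among them.

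The equation also sits among sentences on biochemical variables and cell counts, so its link to NEWS-2 can be questioned. But the sentence that introduces the model applies it to the trial's results generally, and no other model is given for NEWS-2.

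It may be said that baseline is already in the outcome. That answers only the raw-score reading; a change score still has a larger SE than a baseline-adjusted analysis for every r in the assumed range. Nor does the nested random term settle the matter of time. Read as time within hospital, it is shared by both arms and cannot give a treatment effect on a particular day.

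Two stronger inferences are tempting. The first is that the unadjusted comparison is biased. It is not, under randomisation; the cost is precision. The second is that the end-of-treatment effect is diluted by about half. That needs a day-10 target and an effect that grows steadily, and the article states neither. Its rationale expects the intranasal drug to act fast, and the Outcomes section refers to a lasting effect. Under that time course, averaging loses little or gains power.

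**Conclusion.** The point holds as a gap in pre-specification with a conditional cost. Baseline NEWS-2 should be named in the primary model and is not. If it is left out, the SE at a single day is 24% to 8% larger than necessary for a change score and 5% to 40% larger for a raw score, for r from 0.3 to 0.7. These figures assume equal SDs and a continuous score. They do not carry over to the two-point responder outcome, for which no loss has been calculated.

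The time element is a matter of clarity. The article does not say whether the primary contrast is time-averaged or at a named day. A time-averaged coefficient would understate an end-of-treatment effect only if the effect builds up: to 55% of it under linear growth, to 90% if the effect is full by day 3, and not at all if it is constant. The article sets no day-10 estimand, so dilution is not shown.

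**What to change.** State in the Statistical analysis section that the primary NEWS-2 model takes post-baseline NEWS-2 as the response. Its fixed covariates should be baseline NEWS-2, treatment, day (categorical), treatment-by-day, age, sex and weight, with hospital in the model. State whether the primary contrast is the average over days or the difference at a named day, and make the Outcomes section agree. If the two-point improvement is analysed as a responder outcome, specify a logistic model with baseline NEWS-2 and hospital as covariates, and say that the odds ratio is conditional on them.

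The cost is statistical wording only. Baseline NEWS-2 is known at entry and clinical data are already collected daily. The wording should be fixed before outcome data are compared by arm, because the trial is open-label and an open list leaves room to choose covariates afterwards.

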## Methods

### Trial design

The “REVIVAL” trial is an interventional, phase 2, multicenter, open-label, randomized controlled study in adult patients with confirmed COVID-19 diagnosis, designed to evaluate the efficacy (superiority) of low doses of intranasal DXM compared to intravenous administration (allocation ratio 1:1) in patients of five COVID-19 referral centers in Mexico City.

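### The estimator rule (maximum likelihood if the sample is unbalanced) cannot be combined with the Kenward-Roger inference promised in the next sentence

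*Protocol article*

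**What the plan says.** All the relevant text is in the Statistical analysis section of the protocol article, apart from the number of hospitals.

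- **Estimator, balanced case:** "We will perform restricted maximum likelihood (REML) estimation in case we obtain balanced samples".
- **Estimator, unbalanced case:** "However, if we obtain an unbalanced sample, we will use maximum likelihood instead".
- **Inference:** "Because we expect a small sample size from some hospitals, we will make inferences using the Kendward-Roger degrees of freedom method". An F statistic built on an adjusted covariance matrix of the fixed effects follows.
- **Support for the adjustment:** "Simulations studies showed adequate performance of modifications with different REML".
- **Top-level clusters:** the Trial design section enrols "patients of five COVID-19 referral centers in Mexico City". Hospital enters the model as a random effect.
- **Fixed terms:** treatment, age, sex and weight are named, with other confounders left open.

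The section does not say that REML is kept when Kenward-Roger is used, and it does not define what counts as balanced.

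**The concern.** Two adjacent sentences give instructions that conflict in the case most likely to arise. Kenward-Roger inflates the covariance matrix of the fixed effects, and derives denominator degrees of freedom, from a REML fit. If the sample is unbalanced, the first rule imposes ML and the second asks for a correction that an ML fit does not support. The analyst would then have to break one of the two stated rules.

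The switch also has no statistical basis. REML handles unequal cluster sizes as readily as equal ones. It is preferred here because it allows for the fixed effects that have been estimated, and that matters most when there are few clusters. Five hospitals is few. Moving to ML gives up this allowance without gain.

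At stake are an inference rule that can be carried out as written, and a between-hospital variance that is not understated.

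**Working it through.** The protocol gives no figure for this point, so there is none to reproduce. The check has three steps.

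**Step 1. Follow the rules on the likely path.**

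1. The plan expects few patients from some of five hospitals. With 120 patients in total, that implies unequal hospital sizes.
2. Unequal sizes make the sample unbalanced in the usual sense, so the rule selects ML.
3. The plan then calls for Kenward-Roger, and supports the adjustment with simulation work on REML.
4. Kenward-Roger is defined for REML fits. Items 2 and 3 cannot both be carried out.

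The tie between Kenward-Roger and REML is a property of the method, not something the protocol states. The protocol's own supporting sentence is consistent with it.

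**Step 2. Size of the ML bias in the between-hospital variance.**

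*Simple approximation.* With k clusters and one mean estimated, the ML variance is about (k − 1)/k of the REML variance. For k = 5 this is 4/5 = 0.80, or 20% too low.

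*Simulation.* Taken from the protocol: 120 patients, 5 hospitals, 1:1 treatment between patients. Assumed, because the protocol gives no values: hospital variance 0.25, residual variance 1, treatment plus 4 covariates, one response per patient, and hospital sizes of 24 each (balanced) or 60/30/15/10/5 (unbalanced). There were 500 replicates.

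| Hospital sizes | Fit | Mean hospital variance (true 0.25) | Mean residual variance (true 1) |
|---|---|---|---|
| Balanced | REML | 0.245 | 0.996 |
| Balanced | ML | 0.187 | 0.953 |
| Unbalanced | REML | 0.248 | 1.003 |
| Unbalanced | ML | 0.182 | 0.961 |

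Relative to truth, ML gives 0.187/0.25 = 0.748 (25% too low) when balanced and 0.182/0.25 = 0.728 (27% too low) when unbalanced. REML is within 2% in both cases. The ML shortfall is nearly the same in the two settings, so balance is not a reason to choose one estimator over the other.

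**Step 3. Effect on the treatment comparison.**

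To isolate the estimator, both fits are judged against the same critical value, 1.96. This is a device for sizing the effect. The protocol does not plan it.

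*Formula.* At patient level with p fixed effects, the ML standard error is about √((120 − p)/120) of the REML one, and type I error is P(|t| > 1.96 × that ratio) on 120 − p degrees of freedom.

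- p = 5 (intercept, treatment, age, sex, weight): ratio √(115/120) = 0.979, type I error 5.75%.
- p = 10: ratio √(110/120) = 0.957, type I error 6.3%.
- p = 15: ratio √(105/120) = 0.935, type I error 7.0%.

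The protocol does not give the number of covariates. Only the first line uses the terms it names. The other two show what happens if many are added.

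*Simulation, unbalanced sizes as above.* With 500 replicates: 5.8% under ML and 5.6% under REML. With 4,000 replicates: 6.1% and 5.6%. The Monte Carlo standard error at 500 replicates is about √(0.058 × 0.942/500) = 1.0 percentage point, so the longer run is the better guide. It puts the difference at about half a percentage point.

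**The case against.** The strongest reply is that this is a wording conflict with little effect on the result that matters. Treatment varies within hospitals, so the between-hospital variance hardly enters its standard error, and Step 3 bears this out. That stands, and it limits the weight of the point. It does not make the two rules compatible.

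It can also be said that the plan never states that it expects imbalance. It expects few patients from some hospitals, and unequal sizes are an inference from that. The inference is a natural one, but it remains an inference, so the conflict is likely rather than certain.

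A reader might infer more than the document supports:

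- **That the rule is the wrong way round.** The ML bias is about the same in both cases. Balance is irrelevant to the choice, not reversed.
- **That false positives rise sharply.** Large inflation can be shown for a contrast between groups of hospitals. The mixed model specifies no such contrast, and the initial comparison of hospitals is not tied to it.
- **That the analysis will fall back on large-sample z tests.** The protocol does not say so. It leaves open what happens when the two rules collide.
- **That the primary analysis is compromised.** The Outcomes section defines the primary outcome as a two-point NEWS-2 improvement. The REML/ML sentence follows directly on biochemical markers and cell counts. For NEWS-2 components the plan carries the last observation forward in patients with at least two observations, so early death or discharge does not by itself unbalance those series over time. Unequal hospital sizes remain.
- **That ML contradicts the statement "This approach will give unbiased approximation even in presence of unbalanced samples".** That sentence follows the choice of residual covariance structure. Fixed-effect estimates from a Gaussian mixed model are unbiased under ML as well as REML, so the statement is not clearly contradicted.
- **That the estimator can be picked to suit the results.** Balance is undefined, which leaves the trigger loose, but the rule is stated in advance and depends on the structure of the sample, not on outcomes.

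**Conclusion.** The point holds as a conflict between two stated rules and as an unfounded condition on the choice of estimator. If hospital sizes are unequal, the plan requires ML and also a correction that belongs to REML.

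The between-hospital variance would be understated by about 20% on the simple approximation and 25-27% in the simulation. The simulation figures rest on the assumed variances, hospital sizes and covariates, and would change with them. For the treatment contrast the harm is small: type I error of about 6% under ML against 5.6% under REML, both with 1.96 as the critical value, with treatment and a few covariates. It would reach 6.3-7.0% only with 10 to 15 fixed effects, a number the protocol does not give.

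The rule should be corrected because it cannot be carried out as written. It does not threaten the validity of the trial.

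**What to change.** Replace the two sentences on the choice of estimator by one: *All linear mixed models are fitted by REML with Kenward-Roger standard errors and degrees of freedom, whether or not the sample is balanced; ML is used only for likelihood-ratio comparison of models with different fixed effects.*

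This keeps the small-sample inference the plan already intends, agrees with the REML simulation evidence it invokes, and removes the need to define balance. It needs no additional patients or data. The only statistical cost is slightly wider confidence intervals than ML would give.

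### Eta squared, named as the main treatment-effect measure, has no sign or clinical unit and cannot express a superiority result; no signed estimate with a 95% CI is stated as the reported measure

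*Protocol article*

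**What the plan says.** The measure is named near the end of the Statistical analysis section: "All analysis will describe the number of patients with the outcome of interests, the treatment effect (mainly using eta squared". The words at issue are "the treatment effect (mainly using eta squared". The same sentence goes on to additive and multiplicative interactions with 95% confidence intervals, and ends with "the direction of the interaction (positive or negative) by specific subgroups". The only direction it promises is therefore that of the interaction.

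The outcome being measured is described in two ways. The Outcomes section has "clinical improvement, defined as a two-point improvement in the ordinal scale regarding the initial NEWS-2 score", which is a yes/no response for each patient. The Abstract has "defined as a statistically significant reduction in the NEWS-2 score of patients with intranasal versus intravenous dexamethasone administration", which is a comparison of scores.

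On the model, the Statistical analysis section says "we will analyze the results with a multilevel mixed longitudinal model". Treatment is among the fixed effects, estimation is by REML or maximum likelihood, and an F statistic with Kenward-Roger degrees of freedom is given for linear combinations of the fixed effects. The Trial design section states a superiority aim for the intranasal route. The sample size is planned on a difference in proportions, 70% versus 45% free of mechanical ventilation.

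Nowhere does the article name a risk difference, risk ratio, odds ratio or adjusted mean difference as the measure in which the treatment effect will be reported.

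**The concern.** A superiority trial has to report which arm did better, by how much in units a clinician can use, and with what uncertainty. Eta squared gives the proportion of outcome variance associated with treatment. It gives no direction, and its size depends on how variable the patients are as well as on how large the benefit is. If it is the main reported measure, the headline figure for the primary outcome would not say whether the intranasal route helped or harmed, nor how many more patients improved or by how many NEWS-2 points.

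This is a choice that the article makes explicitly. It is not a detail left open for an analysis plan that is not shown.

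**Working it through.** The article attaches no numerical value to eta squared, so there is no stated figure to reproduce. The check is whether the measure can carry the trial's question.

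**Inputs**
- Planning rates of 70% (intranasal) and 45% (intravenous), from Sample size and randomization. These are rates of freedom from mechanical ventilation, not of NEWS-2 improvement, and serve only as an illustration.
- 1:1 allocation, from Trial design.
- A two-point NEWS-2 change, from Outcomes, used below as an illustrative difference between arm means.
- The SD of NEWS-2 is not given. SDs of 2, 3 and 4 are assumed, to show a range.

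**1. Direction (binary outcome)**

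With equal arms, eta squared = [(p1 − p2)² / 4] / [p̄(1 − p̄)], where p̄ is the average of the two rates.
- Intranasal 70%, intravenous 45%: p̄ = 0.575, so (0.25² / 4) / (0.575 × 0.425) = 0.015625 / 0.244375 = 0.064.
- Arms swapped, intranasal 45%, intravenous 70%: p̄ is unchanged and (−0.25)² = 0.25², so the result is again 0.064.

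Signed or ratio measures separate the two cases:
- Risk difference: +25 points versus −25 points.
- Risk ratio: 0.70 / 0.45 = 1.56 versus 0.45 / 0.70 = 0.64.
- Odds ratio: (0.70/0.30) / (0.45/0.55) = 2.85 versus 0.35.

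**2. Clinical unit (score outcome)**

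For a mean difference d with equal arms and common SD, eta squared = (d² / 4) / (d² / 4 + SD²). With d = +2 or −2, d² / 4 = 1:
- SD 2: 1 / (1 + 4) = 0.20
- SD 3: 1 / (1 + 9) = 0.10
- SD 4: 1 / (1 + 16) = 0.059

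The same two-point difference gives values more than threefold apart (0.20 / 0.059 = 3.4), and each value is the same for benefit and harm.

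**3. Relation to the planned model**

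A partial eta squared can be approximated from an F statistic as F·df1 / (F·df1 + df2), and the article specifies such an F statistic. For a single treatment contrast, F is the square of the corresponding t, so the sign is lost in the squaring. A model with random effects fitted by REML or maximum likelihood has no unique partition of sums of squares, and the article does not say which version of eta squared is meant. The treatment coefficient from the same model, by contrast, is signed, is in units of the outcome and has a standard error.

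**The case against.** Four arguments can be made for the plan.

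- **The sentence may concern subgroups only.** It follows the subgroup paragraph and closes with specific subgroups, so this reading is possible. It is the weaker one: the sentence opens with all analysis and lists the treatment effect separately from the interactions. On the narrow reading, the article would name no effect measure at all for the primary comparison.
- **The wording is not exclusive.** Eta squared is the main measure, not the only one. That is true, but no alternative is committed to.
- **The information would still exist.** The same sentence promises the number of patients with the outcome, and the section promises means with SDs or frequencies with percentages. If given by arm, these yield a crude risk difference or ratio, and the model yields a signed coefficient. This argument stands. A reader might infer that the primary result could not be interpreted clinically or pooled with other trials. The documents do not support that, because a signed effect could be derived from what is reported or fitted.
- **Eta squared can be obtained from a mixed model.** This also stands. A reader might infer that the measure is incompatible with the planned model, but the F-based approximation shows otherwise. What remains is that the version is unspecified and the result is unsigned whichever version is used.

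The 95% confidence intervals in the sentence are attached to the interactions. Read generously to cover the treatment effect as well, they would be intervals for an unsigned quantity.

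**Conclusion.** The point holds as a fault in the reporting plan. The article makes eta squared its main treatment-effect measure for all analyses, and that measure cannot show which arm is better: 0.064 for a 25-point advantage and 0.064 for a 25-point disadvantage. Nor does it reflect clinical size, since a two-point NEWS-2 difference gives 0.059 to 0.20 over assumed SDs of 4 to 2. No signed treatment effect with a 95% CI is stated as the reported measure.

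The conclusion rests on reading the sentence as covering all analyses, as its opening words say. The binary illustration uses ventilation rates because the article gives none for NEWS-2 improvement, and the SDs are assumptions. The lack of sign depends on neither.

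The consequence is limited to how the result is reported. The hypothesis tests and the sample size do not depend on eta squared, and direction and size could be recovered from the counts or the model coefficient. The change is worth making because it is easy and concerns the headline result.

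**What to change.** First reconcile the Abstract and the Outcomes section on the primary outcome, because the right measure depends on it. Then state as the main reported treatment effect, with a 95% CI:

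- if the primary outcome is reduction in score, the adjusted mean NEWS-2 difference between arms, taken as the treatment coefficient or contrast from the planned mixed model;
- if it is the two-point improvement, the risk difference together with the risk ratio, from a simple binary analysis.

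Report mortality as a risk difference or risk ratio with its 95% CI. Keep eta squared at most as a supplementary descriptive measure and, if it is kept, say which version is computed.

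The score-reduction option needs only a change of wording, since the planned model already yields the estimate. The linear mixed model does not itself give risk differences or ratios, so the binary measures cost one additional standard binary analysis. The data are already collected, and neither the sample size nor the conduct of the trial changes.
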